BRAC’s EHC program operates in several rural sub-districts *(upazilas)* of Bangladesh. The management structure of the A&T interventions, as delivered through through EHC is illustrated in Figure 1**.** Through the EHC platform, BRAC provides affordable and accessible health services to the poor through frontline workers (FLW): *Shasthya Shebika* (SS, community health volunteers) and their supervisors, the *Shasthya Kormi* (SK, community health workers). In EHC sub-districts, several cadres of workers help shape IYCF demand and practice. The SS and the SK were the front line service providers for A&T in 50 sub-districts with EHC programs who delivered age-appropriate IYCF counseling and support services during home visits, antenatal and postnatal sessions, and health forums. IYCF Promoters (PK) recruited for A&T interventions supported the IYCF work of the SS and SK. All of these FLWs were women. Mobile phones and monthly meetings were used to network these teams of workers within sub-districts and unions. All SS, SK and PK were expected to perform specific tasks during the household visits (Table 1) and were expected to give key messages for infants and young children of different age groups (Table 2).

Typically, SS visit about 250-300 households a month that have children aged 0-23.9 months to provide advice and services, attend monthly refresher training for a day once every month, and sell medicines. Each SK supervises 10-15 SS, prepares monthly registers for the SS, conducts field visits 6 days a week, attends monthly one-day refresher training and does performance review along with the SS, and comes to office one day each month to complete monthly report. The SK is also expected to visit all the households in her catchment area every 6 months. SK in sub-districts involved with BRAC’s EHC program receive an additional monthly honorarium for spending two extra hours per day on IYCF-related activities.

The IYCF promoters (PK) were expected to prepare household lists including children 0-23.9 months of age and pregnant women. Each PK was expected to start working from the residence of SS according to daily work schedule. The catchment area for PK was defined such that: (i) there were not more than 350 children 0-23.9 months of age; (ii) there were not more than 2500 households; and (iii) she could visit children 0-23.9 months of age once in two months.

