| - Enters in her Register all identified pregnant women and children 0-24 months of age in her catchment area. - Immediately informs IYCF Promoters about any new births. - Advices mothers and the families to put the baby to the mother’s breast in one hour of birth. - Confirms giving the baby colostrum. - Encourages mothers and the families exclusive breast feeding (EBF) to the babies 0-6 months of age. - Identifies mothers having problems with EBF and solves, if possible; immediately informs IYCF Promoters about this and follows up if necessary. - Refers mothers having problems with feeding her child to appropriate places if needed for the problems. - Encourages mothers and the families regarding feeding children 7-24 months of age the family foods in addition to breast milk. - Identifies mothers having problems with feeding children 7-24 months of age the family foods in addition to breast milk, solves if possible; immediately informs IYCF Promoters about this and follows up if necessary. | - Conducts health forum. - Provides healthcare during household visits and ensures the following activities: - Follows up SS. - Encourages family planning methods for eligible couples. - Observes DOTS of suspected TB patients. - Pregnancy identification. - Encourages and provides ANC and PNC services to the pregnant women. - Encourages vaccination to the target children and pregnant women. - Registers new births. - Encourages installation and proper use of sanitary latrines. - Ensures use of safe drinking water. - Gives messages regarding importance of hand washing with soap for children and all family members. - Responsibilities during household visits - Registers 0-24 month children identified by SS. - Advices mothers and the families to put the baby to the mother’s breast in one hour of birth. - Advices mothers and the families to feed colostrums to the newborns. - Encourages mothers and the families EBF to the babies 0-6 months of age. - Identifies mothers having problems with EBF and solves, if possible; immediately informs IYCF Promoters about this and follows up if necessary. - Refers mothers having problems with feeding her child to appropriate places if needed for the problems. - Encourages mothers and the families regarding feeding children 7-24 months of age the family foods in addition to breast milk. - Identifies mothers having problems with feeding children 7-24 months of age the family foods in addition to breast milk, solves if possible; immediately informs IYCF Promoters about this and follows up if necessary. | - The household visit schedule of the IYCF Promoter – - 1st visit: within 48 hours of birth. - 2nd visit: within 7-10 days after birth. - 3rd visit: 2 month 1 day – 2 months 29 days. - 4th visit: 5 months 1 day – 5 months 29 days. - 5th visit: 6 months 1 day – 6 months 15 days. - 6th visit: 8 months 16 days – 9 months 15 days. - 7th visit: 12 months 1 day – 16 months 29 days. - 8th visit: 18 months 1 day – 23 months 29 days. - Visits households according to the schedule and - - Enlists children 0-24 months of age. - Encourages mothers and the families exclusive breast feeding (EBF) to the babies 0-6 months of age. - Encourages mothers and the families regarding feeding children 7-24 months of age the family foods in addition to breast milk. - Demonstrate appropriate techniques of feeding breast milk and other family foods to the mothers. - Problem solving related to breast feeding, feeding other family foods and follow up – - Holds forums with mothers regarding health and nutrition education. - If needed, works out of working hours for emergency situation. - Attends training, refresher training and meetings as needed. - Completes daily report forms, prepares monthly report of her catchment area and submits monthly reports to POs. |

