# EVALUATION DESIGN

The impact evaluation of community component A&T interventions delivered through the EHC program uses a cluster-randomized design with repeated cross-sectional surveys at the baseline and endline (Figure 3). For the impact evaluation of A&T’s community-based rural platform, 20 rural subdistricts (*upazilas*) that were part of BRAC’s Essential Health Care (EHC) program platform for A&T were purposively chosen. The objective of this impact evaluation model is to capture the synergistic impact of A&T’s community component along with media communications and private-sector activities, such as the promotion and integration of micronutrient powders.

The impact evaluation is designed to capture impact on all key A&T indicators (stunting, infant and young child feeding (IYCF), and anemia). Using a repeated cross-sectional survey design, impact on stunting will be assessed in children 24-48 months old. The impact on other IYCF practices and anemia will be assessed in children 6-23.9 months old; and the impact on exclusive breastfeeding (EBF) will be assessed in children 0-5.9 months old. A double difference impact analysis as well as analysis by exposure level to interventions will be employed to determine the impact of A&T interventions.

The baseline survey was in April to July 2010, and an endline survey is planned for April to July 2014.

The main outcomes being examined are changes in mean height-for-age Z-score (HAZ) and changes in the prevalence of childhood stunting between baseline and the post-intervention survey. Other core impact indicators for A&T in Bangladesh include changes in age-appropriate WHO-recommended IYCF practices among children under 2 years of age (EBF for children 0-5.9 months old and breastfeeding + age-appropriate complementary feeding for children 6-23.9 months old) and anemia among children 6-23.9 months of age.

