# STATISTICAL ANALYSIS PLAN

## Overall approach

The overall approach to the A&T impact analysis involves two major steps:

1. Accurately **estimate the impact** of the A&T-intensive interventions on IYCF practices and anthropometric outcomes
2. **Enhance plausibility** of impact estimates through:
   1. **Examining social desirability bias** for IYCF practices, especially for those practices (EBF) that are susceptible to systematic reporting bias
   2. Assessment of **biological plausibility** of changes in outcomes based on age of initial exposure and duration of exposure
   3. ***Impact pathway analysis*** that documents exposure to A&T interventions
   4. Analysis of ***trends in underlying determinants*** of IYCF practices and child growth, to rule out alternative reasons for trends over time

The overall analysis will examine and adjust, as needed, both for time invariant characteristics that can have impact on outcomes (i.e., geographic clustering) and time variant determinants where important changes were seen over time (e.g., women’s work patterns, food security, etc.).

The impact on exclusive breastfeeding (EBF) will be assessed in children 0-5.9 months old. The impact on other IYCF practices and anemia will be assessed in children 6-23.9 months old and the impact on stunting will be assessed in children 24-47.9 months old.

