## Detailed statistical analysis approach

The statistical analyses will include intent-to-treat analyses, unadjusted and adjusted, for primary impact indicators. Several other analyses related to establishing plausibility of impacts will also be undertaken.

1. **Impact estimates**

Impact estimates in Bangladesh will be double difference estimates of changes in key impact indicators. This takes into account changes over time between baseline and endline in the intervention and comparison groups, and differences between groups at these times. The impact estimates will yield (1) **percentage point and percentage changes** for IYCF practices and stunting, wasting, and underweight, and anemia (Bangladesh only); and (2) change in **mean Z scores** for height for age, weight for age, weight for height, and hemoglobin (Bangladesh only).

Analyses will be done separately for each critical age group, e.g., exclusive breastfeeding will be assessed only in children 0-5.9 months old, complementary feeding in children 6-23 months old and anthropometry impacts in children 24 months and above. These reflect the different sample age groups for the impact evaluation. All analyses are in Stata.

Analyses will focus on the following:

- ***Pure* *Intent-to-treat*** analyses based on the original evaluation design and original age groups, using child-level data and fixed-effects analysis to achieve double difference estimates. The fixed-effects analysis will account for village, the smallest level repeated between baseline and endline. Further adjustment for geographic clustering at provincial/divisional, district and commune/subdistrict level will be done using random- or fixed-effects to adjust for clustering if needed; the need for this is not likely because of the accounting of variation among villages.
- ***Pure intent to treat in high potential for exposure age groups* –** this analysis will focus on the stunting indicator and capture impact estimates in an age group of children who are mostly likely, because of their age, to have been exposed to A&T’s interventions early in infancy and for the longest duration. This is the 24-35 month age group in both Bangladesh and Vietnam. We will examine the pattern of HAZ across the full 0-59 month age range, and look at impacts on stunting beginning at the age when HAZ begins leveling off i.e. possibly beginning at 18 months of age. We will use fixed-effects regression models to adjust for village clustering as above.

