   1. Examine **anthropometry outcomes by child age (**biological plausibility**) and duration of exposure** (intent to treat analysis for implementation plausibility).

- **Exposure variables** will include the following
  - FLW contact (use the question regarding # of contacts within the last 6 months))
  - Mass media exposure (use both the question of recall of ever having seen specific ads, with recall of at least x number of messages in the ad, or select messages )
  - Franchise contact (VN)
  - **MNP purchase and consumption variables (Bangladesh only)**
    - 1. Every purchase
      2. Total number in the last 6 months
      3. Consumption in last 7 days
- **Plausibility analysis based on impact pathways**
  - Is exposure to A&T interventions greater in A&T-intensive areas?
  - Are IYCF and nutrition knowledge, especially of key messages promoted by the program (“content tracers”) greater in A&T-intensive areas?
  - Are other behavioral determinants more conducive to behavior change in A&T-intensive areas?
  - Is intensity of intervention exposure associated with IYCF? practice/anthropometry outcomes, controlling for confounding factors?
- **Plausibility analysis based on underlying determinants of IYCF/anthropometry:**
  - Are there any systematic differences in underlying determinants of IYCF practices and anthropometric outcomes over time or across groups, such that *differential changes* in those underlying determinants over time offer alternative explanations for changes in IYCF or anthropometric outcomes? For example:
    - In Bangladesh, have there been changes in food security over time, and across groups, that might drive some of the changes in diet diversity?
    - In Vietnam, have there been differential changes in women’s work patterns over time and across groups, in ways that might shape EBF practices differently?
  - This analysis – assessing changes and then adjusting statistically for those underlying differences where changes are seen – will adjust for *time-variant* factors that changed over time.   The geographic clustering in the DID model only adjusts for time *invariant* changes over time.

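### The six-month worker-contact count cannot measure early-life exposure for growth outcomes at 24-47.9 months, so the exposure-intensity analysis of growth would be uninformative

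*Combined protocol and SAP*

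**What the plan says.** **Exposure measure.** Under Detailed statistical analysis approach, Plausibility analysis 2 opens with anthropometry by child age and duration of exposure, then lists exposure variables. For frontline-worker contact the instruction is to "use the question regarding # of contacts within the last 6 months". This is the only worker-contact measure listed for Bangladesh. Mass media exposure, in the same list, is based on ever having seen specific advertisements.

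**Use of the measure.** The impact-pathway questions in the same section include: "Is intensity of intervention exposure associated with IYCF? practice/anthropometry outcomes, controlling for confounding factors". Evaluation Design also announces exposure-level work as part of the design: "A double difference impact analysis as well as analysis by exposure level to interventions will be employed".

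**Age at outcome.** Overall approach states that "the impact on stunting will be assessed in children 24-47.9 months old". Table 6 gives essentially that age group for both HAZ and stunting, and the detailed approach refers to "anthropometry impacts in children 24 months and above". The SAP adds a 24-35 month group with high potential for exposure, and mentions stunting analyses that might start at 18 months.

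**Age at service.** In Description of the Alive & Thrive Program in Bangladesh, the work of the volunteers (SS) and IYCF Promoters (PK) is directed at children aged 0-23.9 months. The last slot in the promoter's schedule (Table 1) is "8th visit: 18 months 1 day – 23 months 29 days". One contact does not depend on the child's age: "The SK is also expected to visit all the households in her catchment area every 6 months".

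**The concern.** An exposure-response analysis of attained height should measure contact at the ages when the programme could have acted on the child's feeding. Here the outcome is measured at 24 months or later, the child-directed visits stop just before 24 months, and the exposure question looks back only six months. For older children in the growth sample, the question covers a period in which no IYCF visit was scheduled for that child.

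Such a mother may still report contacts. They would come from the SK's routine household rounds, whose Table 1 tasks include family planning, tuberculosis treatment, vaccination and sanitation, or from visits made for a pregnancy or another child. None of these is the index child's exposure during the first two years.

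At stake is the plausibility argument for growth. The SAP wants to judge a growth effect partly by age at first exposure and duration of exposure, and a count of recent contacts measures neither. A null result could be read as evidence against a real effect, and a positive one as support for an effect that the data do not show.

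**Working it through.** The plan gives no figure of its own here, so the check sets the age windows against each other.

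**Inputs**
- Look-back: 6 months (Plausibility analysis 2).
- Child-directed service period: birth to 24 months. The last PK visit window runs from 18 months 1 day to 23 months 29 days (Table 1).
- Growth sample: 24-47.9 months, a span of 24 months (Overall approach; Table 6).
- 1,100 children per arm (Sample size and power calculations), used only to scale the shares.
- Assumption: ages uniform within the range, because the documents give no age distribution. This is varied below.

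**Formula.** For a child aged *a* months, with *a* between 24 and 48, the look-back runs from *a* − 6 to *a*. Its overlap with the service period is max(0, 24 − (*a* − 6)) = max(0, 30 − *a*). It is zero from *a* = 30 onward.

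**Share with no overlap, uniform ages**

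| Age group (months) | No overlap |
|---|---|
| 24-47.9 (main growth group) | 18/24 = 75%; 0.75 × 1,100 = 825 per arm |
| 24-35.9 (high potential exposure) | 6/12 = 50% |
| 36-47.9 | 12/12 = 100% |
| 18-47.9 (if analyses start at 18 months) | 18/30 = 60% |

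**What the remaining children contribute.** Those aged 24-29.9 months are 6/24 = 25% of the sample, or 275 per arm. Their look-back can reach only the eighth of the eight scheduled PK visits. Their mean overlap is 3 of 6 months. If the eighth visit is also uniform within its window, it falls inside the look-back for about half of them: 0.25 × 0.5 = 12.5% of the whole sample. Averaged over the sample, overlap is 0.25 × 3 = 0.75 months. That is 0.75/6 = 12.5% of the look-back and 0.75/24 = about 3% of the service period.

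**Sensitivity to the age distribution.** If a share *s* is aged 24-29.9 months, the share with no overlap is 1 − *s*.
- *s* = 20%: 80%, or 880 per arm.
- *s* = 25%: 75%, or 825 per arm.
- *s* = 40%: 60%, or 660 per arm.

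The no-overlap group remains the majority unless at least half the sample is aged 24-29.9 months.

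**The case against.** **The list is open and shared.** The exposure variables are introduced as inclusions, and one list serves both feeding and growth outcomes. No line makes the six-month count the only regressor for HAZ. This stands as a point of wording. Even so, the count is the only worker-contact measure named for Bangladesh, it sits under the anthropometry item, and no other contact window is assigned to growth.

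**Part of the growth analysis may not need reported contacts.** The analysis by child age and duration of exposure is labelled intent to treat and can be read as cohort-based. This stands and limits the point to the exposure-intensity question.

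**Younger children are measured too.** Height is taken on every index child, and below 24 months the count falls within the service period. That is true, but the plan's main growth group remains 24-47.9 months.

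**A better variable may already exist.** Annex 1 has items on home visits received and counseling during them, with no stated recall period, and items on counseling in antenatal care and breastfeeding help around delivery. Household composition is recorded with ages, so a younger child can be identified. This makes the repair easier, but the SAP does not assign any of these items to growth.

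**Stronger readings that the documents do not support.** A reader might infer that all home visits stop at 24 months. They do not, because the SK's household rounds continue. A reader might also infer that a true relationship would be attenuated, or reversed through birth spacing. The documents contain nothing on birth spacing and growth, and the direction of bias cannot be determined from them.

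**Conclusion.** The point holds for the exposure-intensity (plausibility) analysis of growth at 24 months and above. For children aged 30 months or more, the specified variable contains none of the index child's scheduled IYCF visits. That is 75% of the sample under uniform ages, and 60-80% if 20-40% are aged 24-29.9 months. In the 24-35.9 month group it is half, under uniform ages. The result of that analysis could not support or refute a growth effect.

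Two limits apply. The 75% is the share of children whose look-back misses the service period. It should not be read as a misclassification rate, because recent contact may correlate with earlier contact to a degree the documents do not show. Nor does the point touch the main result: the intent-to-treat double-difference estimates for HAZ and stunting, adjusted or not, do not use reported contacts. The six-month count remains reasonable for feeding outcomes in children under 24 months.

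**What to change.** 1. In the SAP, limit the six-month contact count to outcomes in children under 24 months.
2. For HAZ and stunting at 24 months and above, define exposure as the mother's report of IYCF home-visit contact during the index child's first 24 months: whether there was any, and the approximate number. Collect it through a short item in the endline questionnaire, which the Household questionnaire section describes as still in development. The Annex 1 home-visit item would serve instead if its recall period allows.
3. Adjust for the presence of a younger child, using the household composition data.
4. Use village mean contact among households with children aged 0-23.9 months only as a secondary measure. It reflects delivery at endline, not when the children now aged 24-47.9 months were under two. It is also constant within a village, so it cannot be estimated alongside village fixed effects in an endline-only model. Each mean would be imprecise: 500 + 500 = 1,000 under-twos per arm over 100 villages per arm (half of 200) is about 10 children per village.

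**Cost.** SAP wording, a short questionnaire item and one covariate already collected. The downside is longer recall, up to about four years for the oldest children, so the reported number of visits will be approximate. Asking separately about each of the eight Table 1 visit windows would be a heavier module and is not needed for this purpose.

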**Table 6. Impact indicators**

| **Indicator** | **Age group (mo)** | **Remarks** |
| --- | --- | --- |
| ***Breastfeeding practices*** |  |  |
| Early initiation of breastfeeding | 0-23.9 |  |
| Exclusive breastfeeding under 6 months | 0-5.9 | We will also examine questions included in the endline survey that address social desirability bias |
| Continued breastfeeding at 1 year | 12-15.9 |  |
| ***Complementary feeding*** |  |  |
| Introduction of solid, semi-solid food, or soft food | 6-8.9 |  |
| Minimum diet diversity | 6-23.9 |  |
| Minimum meal frequency | 6-23.9 |  |
| Minimum acceptable diet | 6-23.9 |  |
| Consumption of iron-rich food | 6-23.9 |  |
| ***Anthropometry*** |  |  |
| HAZ | 24-47.9.9 | We will also examine impacts on HAZ among potentially fully exposed children (24-35.9 mo.) |
| Stunting | 24-47.9.9 | We will also examine impacts on HAZ among potentially fully exposed children (24-35.9 mo.) |

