# ANNEXES

# Annex 1. Description of modules in household questionnaire

| Module Name | Type of Data Collected |
| --- | --- |
| Household composition | - Basic demographic and socioeconomic data of the household members (name, relation to respondent mother, household head, sex, age, marital status, occupation, current school attendance, highest class has completed) |
| IYCF practices | - Data on core IYCF indicators based on WHO recommendation - Feeding prelacteal (immediately after birth or 3 days after birth) - Feeding colostrums - Feeding problems and care seeking |
| Child health history, feeding during illness and child appetite | - Illnesses during the previous two weeks (fever, cough/cold, fast breathing, diarrhea) - Feeding when child had diarrhea and recovered from illness - Child appetite |
| Pregnancy and postnatal care | - Antenatal care seeking - Using micronutrient supplement during pregnancy - Nutrition/IYCF counseling during ANC - Place of birth, Mode of delivery - Child birth weight - Support during delivery - BF advice/help during or immediately after delivery - Intention to use baby formula |
| Mother’s IYCF knowledge, beliefs andattitudes | - BF: Initiation, Exclusivity and Continuation - CF: Timing of introduction, Frequency, Quantity, Dietary diversity - Responsive feeding (Encourage children to eat) |
| Use of A&T community component program services by mother, father, grandmother (funds permitting) | - Exposure to home visits and counseling services:   - Awareness of and exposure to FLWs   - Received home visits   - Counseled during home visits   - Satisfaction with nutrition counseling services - Exposure to social mobilization |
| Use of micronutrient powder interventions | - Exposure to micronutrient powder interventions, including awareness, purchase and use of MNPs |
| Awareness, trial and adoption of sentinel practices | - Expose to information about BF, CF practices - Trial, adoption and influence factors |
| Child development | - Motor development scale - Language development scale - Early childhood development |
| Mass media | - Expose to TV, radio, - Viewing of advertisements/ information on IYCF - Specific TVC questions (aided recall)   - If viewed   - The most channels usually watch   - Main messages   - Activities follow up after watching the ads   - Opinion about messages and the ads |
| Behavioral Determinants | - Intention to adopt IYCF practices - Belief - Social Norms - Self-efficacy |

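### For early initiation of breastfeeding, the six-month worker-contact count and the recent micronutrient powder variables largely measure exposure after the outcome is settled

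*Combined protocol and SAP*

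**What the plan says.** The second plausibility analysis, under Detailed statistical analysis approach, names these exposure variables for Bangladesh:

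- "FLW contact (use the question regarding # of contacts within the last 6 months";
- mass media, for which the plan will "use both the question of recall of ever having seen specific ads";
- "MNP purchase and consumption variables (Bangladesh only", made up of a purchase item with no time window, the number bought in the last 6 months, and consumption in the last 7 days.

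No antenatal or delivery contact is named. Further down, the same analysis asks: "Is intensity of intervention exposure associated with IYCF? practice/anthropometry outcomes, controlling for confounding factors".

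The Impact indicators section makes the WHO feeding indicators core outcomes. Table 6 lists "Early initiation of breastfeeding" among them, for ages 0-23.9 months. No sentence sets it apart in the exposure analysis.

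Annex 1 shows that the pregnancy and postnatal care module records "Nutrition/IYCF counseling during ANC" and "BF advice/help during or immediately after delivery". Table 4 places prenatal and postnatal care in its row on access, exposure and use of services, and foresees looking at impact trends by level of exposure.

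**The concern.** Table 1 has workers advise that the baby be put to the breast within an hour of birth, so the outcome is fixed at that point. A contact made later cannot have influenced it. A count over the 6 months before interview looks back to the right period only in the youngest infants, and then only in part.

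An association built on such a count is hard to interpret in either direction. Mothers or villages that are generally well served could show both good initiation and many recent contacts. Conversely, Table 1 has the community volunteers (SS) and community health workers (SK) pass feeding problems to the IYCF Promoters (PK) and follow up, so a poor start could itself generate contacts and produce a null or inverse association. Adjustment for confounders does not repair an exposure that comes after its outcome. The SAP intends these analyses to make the impact estimates more plausible, and for this indicator a mis-ordered result would mislead in that role.

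**Working it through.** The plan states no figure for this analysis, so there is none to reproduce. The check is on timing.

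**Inputs**
- Look-back for FLW contacts: 6 months (SAP exposure list).
- Age range for early initiation: 0-23.9 months (Table 6).
- Planned sample per arm: 500 aged 0-5.9 months and 500 aged 6-23.9 months (Sample size and power calculations). These agree with the stated total: 2 × (500 + 500 + 1,100) = 4,200.
- Assumed: the early-initiation sample is these two groups together; ages are uniform within each group; the first hour of life is treated as the moment of birth.

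**Share of window time after birth.** For a child aged a months it is min(a, 6)/6.
- 6-23.9 months: 6/6 = 100%. These children are 500/(500 + 500) = 50% of the sample.
- 0-5.9 months: mean age 3 months, so 3/6 = 50% on average.
- Planned 500:500 sample: 0.5 × 50% + 0.5 × 100% = 75%.
- If ages were instead uniform over 0-24 months: (6/24) × 50% + (18/24) × 100% = 87.5%.

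**Share of actual contacts after birth.** Let k be the antenatal contact rate divided by the postnatal rate. The documents do not give k, so it is varied. The average window in the 500:500 sample holds 0.5 × 3 + 0.5 × 6 = 4.5 months after birth and 0.5 × 3 = 1.5 months before it. The share is 4.5/(4.5 + 1.5k). With uniform ages the figures are 5.25 and 0.75 months, and the share is 5.25/(5.25 + 0.75k).

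| k | 500:500 sample | Uniform 0-24 months |
| --- | --- | --- |
| 0 | 100% | 100% |
| 0.5 | 86% | 93% |
| 1 | 75% | 87.5% |
| 2 | 60% | 78% |
| 3 | 50% | 70% |

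The share falls to one half at k = 4.5/1.5 = 3, or k = 5.25/0.75 = 7 with uniform ages. In infants 0-5.9 months alone it is 3/(3 + 3k): 50% at k = 1 and 25% at k = 3.

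**MNP variables.** The 6-month purchase count has the same window as the contact count. The 7-day consumption item lies wholly after birth for every child older than a week. The undated purchase item cannot be placed before or after the birth.

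**The case against.** The strongest reply is that the plan never says it will do this. The exposure list stands under a step about anthropometry by child age and duration of exposure. The feeding question is a later bullet that names no variables. The hypotheses under Objectives describe feeding practices as exclusive breastfeeding, or breastfeeding with complementary feeding, and early initiation enters only through Table 6. The list is introduced in open wording, and Table 4 already counts prenatal care as exposure data. All of this is correct, and it makes the point a small one. It does not remove it: this is the only definition of exposure in the SAP, early initiation is a core feeding indicator, and no exposure suited to a birth outcome is assigned to it.

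A reader might also infer from the IYCF Promoter schedule, which opens with "1st visit: within 48 hours of birth" and dates all eight visits from birth, that the whole sample is affected. The documents do not support that. The planned variable is contact with any frontline worker, and the programme description has SS and SK delivering counselling at antenatal as well as postnatal sessions. Their antenatal contacts can fall inside the window for infants under 6 months.

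Nor does every listed exposure follow the outcome. Recall of ever having seen an advertisement carries no date and may precede the birth.

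**Conclusion.** The point holds for the worker-contact count and the MNP variables, applied to one indicator in a supporting analysis. For children aged 6-23.9 months, half of the planned sample, no counted contact can precede early initiation; this needs no assumption about contact rates. For infants 0-5.9 months about half of the window is after birth on average, which gives about 75% of window time overall. That figure rests on uniform ages and the 500:500 split. The share of contacts, as opposed to time, ranges from 100% to 50% as the assumed rate ratio goes from 0 to 3.

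It might be inferred that the impact result for early initiation is compromised. It is not: the intent-to-treat double difference compares randomised areas over time and uses none of these variables. What is at risk is only the reading of the exposure association for this indicator. The gap is in the analysis plan and not in data collection, and it is minor.

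**What to change.** In the exposure list of the second plausibility analysis, state that for early initiation the 6-month contact count and the MNP variables are not used, and that the main exposure is infant-feeding counselling during antenatal care. Refer to the pregnancy module and to the prenatal care entry in Table 4. Use the delivery item only as a secondary exposure, because it also covers help just after delivery and so may follow initiation.

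The cost is a sentence or two in the SAP, with no new data. There are two drawbacks to disclose. Antenatal counselling is recalled over up to about 2 years, although early initiation itself is recalled over a similar span at 0-23.9 months. And Annex 1 does not tie the antenatal item to the programme's own workers, so it may capture counselling from elsewhere and should not be described as programme exposure without that caveat.
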